## Abstract

**Background:**

Adolescents living with HIV (ALHIV) have worse health outcomes than other populations of people living with HIV. Contributing factors include lack of standard and comprehensive procedures for ALHIV transitioning from pediatric to adult care. This has contributed to poor retention at, and following transition, which is problematic especially in high ALHIV-burden, resource-limited settings like Nigeria.

**Methods:**

Using a two-arm cluster randomized control design, the Adolescent Coordinated Transition (ACT) trial will measure the comparative effectiveness of a graduated transition and organized support group intervention against the usual practice of abrupt transfer of Nigerian ALHIV from pediatric to adult care. This study will be conducted at 12 secondary and tertiary healthcare facilities (six intervention, six control) across all six of Nigeria’s geopolitical zones. The study population is 13- to 17-year-old ALHIV (*N* = 216, *n* = 108 per study arm) on antiretroviral therapy. Study participants will be followed through a 12-month pre-transfer/transition period and for an additional 24 months post transfer/transition. The primary outcome measure is the proportion of ALHIV retained in care at 12 and 24 months post transfer. Secondary outcome measures are proportions of ALHIV achieving viral suppression and demonstrating increased psychosocial wellbeing and self-efficacy measured by psychometric tests including health locus of control, functional social support, perceived mental health, and sexual risk and behavior.

**Discussion:**

We hypothesize that the ACT intervention will significantly increase psychosocial wellbeing, retention in care and ultimately viral suppression among ALHIV. ACT’s findings have the potential to facilitate the development of standard guidelines for transitioning ALHIV and improving health outcomes in this population. The engagement of a consortium of local implementing partners under the Nigeria Implementation Science Alliance allows for nationwide study implementation and expedient results dissemination to program managers and policy-makers. Ultimately, ACT may also provide evidence to inform transitioning guidelines not only for ALHIV but for adolescents living with other chronic diseases in resource-limited settings.

**Trial registration:**

ClinicalTrials.gov, ID: NCT03152006. Registered on May 12, 2017.

**Electronic supplementary material:**

The online version of this article (doi:10.1186/s13063-017-2347-z) contains supplementary material, which is available to authorized users.

## Background

Between 2005 and 2012, global acquired immunodeficiency syndrome (AIDS)-related deaths fell by 30% among people living with human immunodeficiency virus (HIV); however, mortality among adolescents living with HIV (ALHIV) increased by 50% in the same period [1]. Nearly 92% of these deaths occurred in sub-Saharan Africa, where AIDS is the leading cause of mortality among adolescents [2–4]. Of the estimated 1.75 million ALHIV in sub-Saharan Africa, approximately 240,000 are living in Nigeria, which represents the second highest burden of adolescent HIV globally [2]. In 2013, an estimated 11,000 deaths occurred among Nigerian ALHIV, representing 9.2% of AIDS-related deaths among all African adolescents [2].

Loss to follow-up (LTFU) and poor retention in care are associated with increased risk of mortality and morbidity among ALHIV [5, 6]. Studies have demonstrated that LTFU rates are higher and retention lower among ALHIV, compared to adult patients [6, 7]. A recent nationwide study reported a LTFU rate among Nigerian ALHIV at 16.1% after a mean follow-up of 28 months [8]. In addition to LTFU, poor adherence to antiretroviral therapy (ART) results in virologic treatment failure and contributes to increased mortality among adolescents [9–11].

The healthcare transition period is particularly high risk for LTFU and other poor health outcomes among ALHIV. Healthcare transition is defined as “the purposeful, planned movement of adolescents and young adults with chronic physical and medical conditions from child-centered to adult-oriented healthcare systems” [12]. Barriers to successful transition have been categorized as: (1) patient/family related (e.g., knowledge deficits in self-management skills); (2) provider-related (e.g., lack of time for transitioning, confusion about roles, and pediatricians’ belief that adult providers would provide inadequate care); and (3) system-related (e.g., lack of formal transitioning program, lack of trained adult providers to competently care for transferred adolescents, and challenges in establishing an interdisciplinary team) [13].

A recent nationwide survey conducted by our study group determined that Nigerian ALHIV are routinely transferred from pediatric to adult care at age 15 or 18 years [14]. Factors limiting successful transition and post-transition retention include: lack of preparation, poor logistics, poor communication between pediatric and adult providers, loss of the “pediatric family” relationships of ALHIV, transition readiness and system-related issues such as access to care, and continuity of care post transition [15].

The most commonly identified components of successful transition include: provision of psychological support to help adolescents deal with anxieties and anger, provision of information, e.g., on risky sexual behavior and access to/navigation of medical services, and providing education on disease state and the importance of adherence to treatment [16–21]. Nigerian ALHIV are also reported to seek social support as a coping strategy for stress related to visiting the hospital and taking drugs regularly [22]. Additional factors that promote successful healthcare transition for ALHIV include: open communication between pediatric and adult staff, peer educator support, access to tailored HIV information, and capacity-building for ALHIV to meet their own psychosocial needs especially in self-efficacy and self-esteem [4, 16–20].

While national policy documents in Nigeria recognize HIV among adolescents as an important issue, none of them address healthcare transition and no guidelines exist for transition of Nigerian adolescents living with HIV or, for that matter, any chronic health condition [23, 24]. Therefore, there is an urgent need to develop a feasible, acceptable, and sustainable model of healthcare transitioning for adolescents in Nigeria. Nigeria’s healthcare system remains weak, and HIV care is predominantly foreign donor-supported [25]. Any new intervention or program should require relatively little additional external funding. Thus, the intervention we propose, Adolescent Coordinated Transition (ACT), is designed to integrate well with, and exert leverage on, the existing healthcare system whilst incorporating effective strategies for healthcare transition.

### Conceptual framework

The ACT intervention relies on the social cognitive theory (SCT) (Fig. 1). Although we considered other frameworks such as the Health Belief Model and the Ecological Model, the constructs of the SCT are particularly relevant to HIV/AIDS treatment and risk reduction among adolescents. Many identified challenges lie with the adolescent or within their environment. SCT recognizes that health behavior is influenced by factors within the person (knowledge of the importance of HIV treatment, how to access treatment during transition, and self-efficacy for service utilization in adult clinics) as well as facilitators or barriers within a person’s social and structural environment (the HIV clinic, peers, or support groups).

**Fig. 1 Fig1:**
[figure not shown]
Overview of the social cognitive theory

### Study objectives and hypotheses

This study’s primary objective is to measure the comparative effectiveness of the ACT intervention versus usual care on post-transfer retention in care among ALHIV at 12 and 24 months post transfer. The ACT intervention encompasses a graduated transition period coordinated with an organized support group, which aims to increase retention rates among ALHIV after transfer to adult care. The coordination denotes a complementary pediatric-adult team approach to support the clinical and psychosocial health of the transitioning ALHIV. The graduated transition provides an extended period of time for the transitioning ALHIV to become familiar with adult care while separating from pediatric care. A transition period, rather than abrupt transfer, minimizes the grief associated with the loss of the pediatric “family” and maximizes opportunities for the ALHIV and adult care providers to establish trusting relationships. The ACT intervention is to be compared to the usual care which is abrupt transfer of ALHIV to adult care with neither a transition period nor an organized support group.

ACT’s secondary objectives are:To measure the comparative effectiveness of the ACT intervention versus usual care on post-transfer viral suppression rates among ALHIV at 12 and 24 months post transferTo measure the comparative effectiveness of the ACT intervention versus usual care on psychosocial wellbeing as measured by psychometric tests at 12 and 24 months post transfer

We hypothesize that:Compared to those exposed to usual care, ALHIV exposed to the ACT intervention will have significantly higher rates of retention in careCompared to those exposed to usual care, ALHIV exposed to the ACT intervention will have significantly higher rates of viral suppression and higher scores on psychometric testing indicating better psychosocial wellbeing

### Formative consultations

Key information that shaped the design of this study came from multiple formative consultations across the Nigeria Implementation Science Alliance (NISA), a collaboration of the 20 largest HIV implementing partners in Nigeria supported by the President’s Emergency Plan for AIDS Relief (PEPFAR) [26]. NISA-wide consultations held with experienced Nigerian healthcare providers highlighted lack of a transition process for adolescents with common chronic illnesses in Nigeria. There are no guidelines or standard practices for healthcare transitioning for sickle cell anemia, diabetes, asthma, or HIV in Nigeria. As such, the standard of care either is absent or varies widely between providers, healthcare facilities and different parts of the country.

During recent assessments for the establishment of PEPFAR-supported adolescent HIV clinics across NISA’s network, we consulted with Nigerian ALHIV. We found ALHIV eager to be involved in their own healthcare including transitioning; however, they uniformly expressed feeling more comfortable in pediatric care because of time and attention rendered to them. Lessons learned from these consultations (e.g., the need for adult care providers to establish trust with ALHIV, a transition period and not abrupt transfer, and adolescent-friendly psychosocial support) provided critical contextual data to inform our intervention.

## Methods

### Study design

The study is a two-arm, cluster-randomized controlled trial that compares the effectiveness of a graduated, coordinated healthcare transition plus organized support group intervention with the usual care of abrupt transfer among ALHIV. ACT adopts the Type 1 Hybrid Design described by Curran and colleagues, which tests the effect of an intervention on relevant outcomes while observing and gathering information on the implementation of the intervention [27]. The Type 1 Hybrid Design integrates impact and process evaluation with the dual goal of testing intervention effectiveness while identifying factors influencing implementation in context. ACT’s intervention effectiveness will be addressed through measurement and analyses of the primary and secondary objectives. Intervention implementation will be measurement utilizing the RE-AIM framework as a guide for implementation indicators (described in detail below) [28].

### Study setting

The ACT trial is a nationwide study that will be conducted across all six geopolitical zones of Nigeria, namely, the north-west, north-east, north-central, south-west, south-south and south-east zones. Two study sites were selected from each zone to ensure that the intervention is generalizable across the country and can be scaled up expediently if proven effective. The ACT trial is to be implemented by five PEPFAR implementing partners who are NISA members: APIN Public Health Initiatives Limited (APIN), the Center for Clinical Care and Clinical Research Nigeria (CCCRN), Centre for Integrated Health Programs (CIHP), FHI 360 Nigeria, and the Institute of Human Virology Nigeria (IHVN). Collectively, these five organizations support more than 850 comprehensive HIV treatment clinics in multiple settings across Nigeria and provide HIV services to over 24,000 ALHIV of 10 to 19 years old.

### Site selection and randomization

Study sites were selected from among secondary- and tertiary-level PEPFAR-supported healthcare facilities with at least 12 months’ experience in providing comprehensive HIV care and treatment services. Eligible sites were further expected to meet the following criteria:At least 20 ALHIV enrolled in care as of 31 July 2016Separate pediatric and adult HIV care teams and clinicsAt least one dedicated physician and one dedicated nurse for each pediatric and adult HIV clinic

All sites were assessed using a standardized tool to determine whether they met the selection criteria.

Our desire was to meet the suggestions of the Consolidated Standards of Reporting Trials (CONSORT) “extension for cluster designs” checklist in our randomization procedure. To that end, we provide details here of both sequence generation and allocation [29]. Twelve healthcare facilities were selected and randomized 1:1 to the intervention and control arms (Fig. 2). These 12 study sites were pair-matched by geographic location and level of care and then randomly assigned to the intervention group (IG) or to the control group (CG). Particular attention was paid to remove bias of group assignment by concealment at the individual participant level. The randomization of facilities was carried out using scripting language in R (v. 3.3.2) by the project statistician [30]. We first created a random number between 1000 and 10,000 and used the result to seed the group assignment so that the results would be reproducible. Based on the pair-matched locations and level of care, we used the “sample” function to determine which member of each matched facility pair would be assigned to each of CG and IG. Of note, age at transfer for each study site was considered in order to include sites that transferred at 15 years as well as 18 years, according to the results of our survey [14]. All enrolled study participants receiving care at each study site will follow the procedures of their respective randomization arms described below.

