### Participant recruitment

The Standard Protocol Items: Recommendations for Interventional Trials (SPIRIT) Figure includes the timeline for study enrollment, intervention, and assessment (Fig. 4). Study participants will be recruited and enrolled onsite at the 12 study sites. Staff of the five participating local organizations will work with study site staff to identify eligible participants. The site staff will create a master list of eligible ALHIV aged between 13 and 17 years who are enrolled in HIV care at their specific site. Parents and guardians of eligible participants will be briefly informed about the study, and after indicating interest, will be approached by trained ACT research assistants for written informed consent at routine clinic visits during the recruitment period. Research assistants will thoroughly explain all study procedures and obtain consent. Assent will be obtained from eligible 13- to 17-year-old ALHIV wards of consenting parents/guardians. Written informed consent will be obtained from eligible ALHIV under 18 years old who are deemed mature or emancipated minors and meet the following criteria: have been granted the status of adulthood by a court order; have lived independent of parental guidance for a minimum of 1 year; are married; are living on the streets; or are the head of their household [32]. It is expected that recruitment will be completed between 1 July and 1 December 2017 (Additional file 1).

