### Sample size estimation

The design requires two arms (control = direct transfer without transition period or OSG and intervention = graduated transition with OSG). Six geopolitical zones are included in the design, with two sites (one replicate per arm) located in each zone. The factors considered for the sample size estimate are: at least 80% power, assuming 20% effect size, a confidence level of 95%, a correlation among repeated measures of 0.3, and an intra-class correlation within clusters of 0.05. Further, we assume equal numbers of clusters between CG and IG, and clusters within those conditions to be of equal size. Based on these assumptions, a baseline number of 15 participants per site was needed. This was, however, adjusted for several assumed losses. Based on knowledge of healthcare in this area and among target participants, the following participant loss estimates were made: healthcare transfers out of study sites at 5%, participant moving out of study area at 5%, deaths during the study at 7%, and study withdrawal/dropout at 5%. This results in a total of 22% dropouts, requiring an additional three participants (15 × 0.22) for a total of 18 participants per site. Additionally, we anticipate a 30% rate for declining to participate. Hence, we will need to approach an additional five ALHIV (18 × 0.3) for a total of 23 ALHIV currently enrolled as taking ART at study initiation to ensure that the requirement of 18 participants per site is met. Therefore, for two arms across six zones, we have a recruitment goal of 276 ALHIV (23 × 2 × 6) with a desired final sample size of 216 ALHIV (18 × 2 × 6) consented to participate. Sample size estimation was performed using G*Power (v. 3.1.9.1, Universität Düsseldorf, Germany) and Sampsize (v 0.6, P. Glaziou, ampsize.sourceforge.net) with appropriate adjustments for cluster randomization [44].

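### The article claims individual-level concealment, but facilities were randomised before site staff listed and recruited adolescents, and nothing described would provide it

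*Protocol article*

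**What the plan says.** Under Site selection and randomization, the Protocol article reports allocation as already done: "Twelve healthcare facilities were selected and randomized 1:1 to the intervention and control arms". The project statistician drew it in R from a random seed, within pairs matched on location and level of care. Arm then follows site: "All enrolled study participants receiving care at each study site will follow the procedures of their respective randomization arms". The same section makes the claim at issue: "Particular attention was paid to remove bias of group assignment by concealment at the individual participant level".

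Under Participant recruitment, enrolment lies in the future and takes place at the sites: "Study participants will be recruited and enrolled onsite at the 12 study sites". On who finds participants, it says: "Staff of the five participating local organizations will work with study site staff to identify eligible participants", and "The site staff will create a master list of eligible ALHIV aged between 13 and 17 years". Parents and guardians hear briefly about the study and, "after indicating interest, will be approached by trained ACT research assistants for written informed consent". Trial status gives a start in the week of 26 June 2017 and an expected end on 1 December 2017.

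Under Sample size estimation, "we anticipate a 30% rate for declining to participate", with 23 adolescents approached per site to enrol 18. Under Statistical analysis, retention is first compared by a test of proportions without covariates. A Poisson model that can take covariates is to be explored, with age and time since HIV diagnosis as examples.

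**The concern.** In a cluster trial, drawing the allocation properly protects the assignment of facilities. It does not protect the choice of individuals when they are identified and consented after their facility's arm is settled. That second step needs its own safeguard, such as a list fixed before allocation is disclosed or recruiters who do not know the arm. The article claims protection at the individual level and describes neither.

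The primary outcome makes this matter. Willingness to join a study, and ease of contact at routine visits, are plausibly related to later attendance, which is how retention is measured. The two arms also invite families to different things: accompanied alternating visits and a monthly peer group, or usual care. If the arms enrol adolescents who differ in engagement, the retention difference mixes selection with the intervention effect, and an unadjusted test cannot separate them.

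**Working it through.** **Sequence, from the article's own sections**

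1. Site selection and randomization: the 12 facilities are already allocated, and every enrolled participant takes the arm of the site.
2. Participant recruitment and Trial status: listing, approach and consent follow, on site, from late June to 1 December 2017.
3. Description of the ACT intervention: the support group starts at enrolment, so the arm is visible on site from the first participant while recruitment continues.
4. Study staff recruitment and training: each intervention facility names a patient advocate for a case management team. Site-level training covers recruitment together with setting up the support group.
5. Inclusion and exclusion criteria: the exclusion for medical instability leaves room for judgement.

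That recruiting staff know the arm is an inference from items 3 and 4. It is a strong one, but the article does not state it.

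**The article's recruitment figures, reproduced**

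- Losses: 15 × 0.22 = 3.3, taken as 3, so 15 + 3 = 18 per site.
- Refusals: 18 × 0.3 = 5.4, taken as 5, so 18 + 5 = 23 per site.
- Totals: 18 × 2 × 6 = 216 enrolled and 23 × 2 × 6 = 276 approached.
- Share of those approached who do not enrol: 5/23 = 21.7%.

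**Illustration of size**

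The article gives no retention rate by engagement, so these inputs are assumptions: no true effect; 70% of the adolescents approached are engaged and 30% less so; one arm enrols every engaged adolescent first; the other arm enrols a representative group.

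- Engaged among 23: 0.70 × 23 = 16.1.
- Less engaged needed to reach 18: 18 − 16.1 = 1.9.
- Engaged share in the selected arm: 16.1/18 = 0.894, against 0.70 in the representative arm.
- Spurious difference = (0.894 − 0.70) × (retention if engaged − retention if less engaged).

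| Assumed retention, engaged v less engaged | Selected arm | Representative arm | Spurious difference |
|---|---|---|---|
| 80% v 70% | (16.1 × 0.80 + 1.9 × 0.70)/18 = 78.9% | 77.0% | 1.9 points |
| 80% v 60% | (16.1 × 0.80 + 1.9 × 0.60)/18 = 77.9% | 74.0% | 3.9 points |
| 85% v 55% | (16.1 × 0.85 + 1.9 × 0.55)/18 = 81.8% | 76.0% | 5.8 points |

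The article gives its planned effect as 20% without saying on what scale. Read as 20 percentage points, the illustration is 1.9/20 to 5.8/20, about a tenth to three tenths of it. If both arms select alike, the difference is zero. If only the control arm selects, the sign reverses.

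**The case against.** The concealment sentence speaks of bias in group assignment, not in enrolment. Because arm follows site, no one can steer an individual adolescent into an arm, and on that reading the sentence is unclear rather than false. This stands as far as it goes. However, the section sets out to give the details of sequence generation and allocation in line with the CONSORT cluster extension, and it names no mechanism for protection at the individual level.

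Safeguards do exist. There is a master list, consent is taken by trained research assistants, and everyone must already be in care and on ART, which narrows the range of engagement. These reduce the room for selection. They do not make the list independent of the allocation.

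Several stronger readings are tempting and should not be adopted:

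- **That control families are offered nothing.** They are offered usual care, with all adult-clinic services including any adult support groups, and the same study assessments as the intervention arm.
- **That the order of approach is uncontrolled.** The article gives no rule, but a full protocol commonly would, so its absence here is no finding.
- **That nothing in the analysis addresses the problem.** The Poisson model can include covariates. Its weakness is that it is only to be explored, and neither of its example covariates is viral load or prior engagement.
- **That the bias could be much larger.** Applying a literal 30% non-enrolment to the same assumptions gives 0.30 × (0.10 to 0.30) = 3 to 9 points, but that does not match 18 enrolled of 23. If 3 of the 5 not enrolled at each intervention site would not have been retained, the difference is 5.6 to 11.1 points for retention of 60% to 80%. That share is arbitrary: at 80% retention, 1 of 5 would be expected by chance.

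**Conclusion.** The point holds in this form: the article claims individual-level concealment that its described sequence does not support, and differential enrolment by arm can bias the retention comparison. A reader might go further and infer that staff demonstrably knew the allocation, or that concealment certainly did not exist. The documents do not establish that, because lists could have been locked before allocation was disclosed, or recruiters blinded, without the article saying so.

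The direction of any bias is unknown, and so is its size. The figure of about 2 to 6 points rests on invented retention rates and on full selection in one arm with none in the other. It shows that the bias need not be negligible beside the planned effect, and it is not an estimate of what will happen. The sample size is unaffected.

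**What to change.** 1. **Correct the concealment sentence.** Say that allocation was by facility, before recruitment. Do not claim individual-level concealment unless master lists were locked before allocation was disclosed or recruiters were blinded; if either was done, say so.
2. **Adjust the confirmatory comparisons.** Make the retention and viral suppression comparisons adjust for enrolment age and enrolment viral load, keeping the clustering and the matched pairs. Age is already used for eligibility, and Table 1 already schedules viral load at enrolment in both arms. State that this reduces but cannot remove selection on unmeasured engagement.
3. **Report enrolment by arm.** Extend the RE-AIM Reach count, which already covers willingness to participate, to aggregate numbers listed, approached, declined and enrolled in each arm. Take no chart data from those who declined, since data collection begins only after consent or assent.

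The cost is slightly more analysis work and a weaker stated claim about bias. No extra participants, visits or samples are needed. Items 1 and 2 remain possible after recruitment has closed, and so does item 3 wherever sites kept the counts.
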